## Study population

Patients who meet ALL the following inclusion criteria and who do not meet any of the following exclusion criteria are allowed to be enrolled:

Inclusion criteria

1. Age equal to or above 18 years
2. Male or female gender
3. In case of women, unwillingness to remain pregnant during the study period.
4. Written informed consent provided by the patient or by one first-degree relative/spouse in case of patients unable to consent
5. Confirmed infection by SARS-CoV-2 virus
6. Findings in chest-X-ray or in chest computed tomography compatible with lower respiratory tract infection
7. Plasma suPAR ≥6ng/ml

Exclusion criteria

- Age below 18 years
- Denial for written informed consent
- Any stage IV malignancy
- Any do not resuscitate decision
- Presence of respiratory failure as defined in Appendix V
- Αny pO_2_/FiO_2_ ratio less than 150
- Any need for CPAP or mechanical ventilation
- Any primary immunodeficiency
- Less than 1,500 neutrophils/mm^3^
- Known hypersensitivity to anakinra
- Oral or IV intake of corticosteroids at a daily dose equal or greater than 0.4 mg prednisone for a period greater than the last 15 days.
- Any anti-cytokine biological treatment the last one month
- Severe hepatic failure
- Severe renal failure
- Pregnancy or lactation. Women of child-bearing potential will be screened by a urine pregnancy test before inclusion in the study

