## Screening for eligibility

No study related procedure will be performed prior to obtaining written informed consent form. Screening follows these next steps:

- Step 1: The patient is screened for the exclusion criteria. If he meets any of them, he cannot be enrolled. If he does not meet any of them, he remains eligible and screening proceeds to Step 2
- Step 2: The patient is screened for inclusion criteria 1 to 6. If he meets these criteria, he remains eligible and screening proceeds to Step 3.
- Step 3: 18 ml of whole blood is drawn after venipuncture of one forearm vein under aseptic conditions and collected into one EDTA-coated and one non-EDTA-coated tube. The first tube is centrifuged for plasma collection. A commercialized quick blood test with suPARnostic® Quick Triage (Virogates S/A, [name]) will take place, to determinate in a very short time (20 min) suPAR levels in human EDTA-plasma. The sample (100 μl of plasma) will be incubated and handled, according to the manufacturer’s instructions, attached to a provided reader and the results will be displayed through LF Software. The measurement is the result of a lateral flow immunoassay (LFIA) and constitutes a quantitative measurement (in ng/ml) of plasma suPAR levels, provided that suPAR values are detected within the range of 2-15 ng/ml, to be considered accurate. If suPAR is found ≥6 ng/ml, the patient can be enrolled in the study. Blood analysis from blood collected in the second tube will be done as described at the section Laboratory Procedures

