## Patients’ visits and interventions (Appendix II)

*Day 1*

This visit will take place on the morning of the day of the start of treatment with the study drug. The following procedures will be done on that day:

- Recording of co-morbidities, co-administered drugs, past-history, SOFA score (Appendix III), absolute blood cell count and differential (if available) and biochemistry (if available)
- Scoring of the respiratory symptoms (Appendix IV).
- Administration of the study drug
- Recording of adverse events (AE) and severe adverse events (SAE)

*Day 2*

This visit will take place on the morning of the second day from the start of treatment with the study drug. The following procedures will be done on that day:

- Recording of co-administered drugs, absolute blood cell count and differential (if available) and biochemistry (if available)
- Recording of the presence or not of SRF (Appendix V)
- Recording of adverse events (AE) and severe adverse events (SAE)
- Administration of the study drug
- The visit may take place by phone call or through the internet in case of hospital discharge

*Day 3*

This visit will take place on the morning of the third day from the start of treatment with the study drug. The following procedures will be done on that day:

- Recording of co-administered drugs, absolute blood cell count and differential (if available) and biochemistry (if available)
- Recording of the presence or not of SRF (Appendix V)
- Recording of adverse events (AE) and severe adverse events (SAE)
- Administration of the study drug
- The visit may take place by phone call or through the internet in case of hospital discharge

*Day 4*

This visit will take place on the morning of the fourth day from the start of treatment with the study drug. The following procedures will be done on that day:

- Recording of co-administered drugs, absolute blood cell count and differential (if available) and biochemistry (if available)
- Recording of the presence or not of SRF (Appendix V)
- Recording of adverse events (AE) and severe adverse events (SAE)
- Administration of the study drug
- The visit may take place by phone call or through the internet in case of hospital discharge

*Day 5*

This visit will take place on the morning of the fifth day from the start of treatment with the study drug. The following procedures will be done on that day:

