- Recording of co-administered drugs, absolute blood cell count and differential (if available) and biochemistry (if available)
- Recording of the presence or not of SRF (Appendix V)
- Recording of adverse events (AE) and severe adverse events (SAE)
- Administration of the study drug
- The visit may take place by phone call or through the internet in case of hospital discharge

*Day 10*

This visit will take place on the morning of the tenth day from the start of treatment with the study drug. The following procedures will be done on that day:

- Recording of co-administered drugs, absolute blood cell count and differential (if available) and biochemistry (if available)
- Recording of the presence or not of SRF (Appendix V)
- Recording of adverse events (AE) and severe adverse events (SAE)
- Administration of the study drug
- The visit may take place by phone call or through the internet in case of hospital discharge

*Day 14*

This visit will take place on the morning of the 14^th^ day from the start of treatment with the study drug. The following procedures will be done on that day:

- Recording of co-administered drugs, SOFA score (Appendix III), absolute blood cell count and differential (if available) and biochemistry (if available)
- Scoring of the respiratory symptoms (Appendix IV).
- Recording of the presence or not of SRF (Appendix V)
- Recording of adverse events (AE) and severe adverse events (SAE)
- The visit may take place by phone call or through the internet in case of hospital discharge

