# STUDY ENDPOINTS

## Primary study endpoint

The primary study endpoint is the rate of patients who will develop SRF (see Appendix V for definition) until day 14. Patients dying before study visit of day 14 are considered achieving the primary endpoint.

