**STATISTICAL ANALYSIS PLAN (5 October 2020)**

The study is powered for the primary endpoint making the hypothesis that 60% of patients with lower respiratory tract infection due to COVID-19 and suPAR≥6 ng/ml upon hospital admission will develop SRF. To decrease this to 45% with power of 90% at a 5% level of significance, two hundred sixty (260) patients need to be enrolled. Taking into consideration, the single-arm study design, 500 patients should be enrolled to make results more robust. Data will be analyzed for the intention-to-treat (ITT) population.

An interim analysis will be conducted after completion of the 30-day follow up of the first 130 patients, i.e. 50% of the number of patients needed to be enrolled as calculated by power analysis. Parallel comparators receiving standard-of-care treatment (SOC) will be used all patients hospitalized at the same time period in eight departments of Internal Medicine in tertiary hospitals of Athens who were participating in the registry of the Hellenic Sepsis Study Group without participating in the SAVE trial ([www.sepsis.gr](http://www.sepsis.gr)). Data and biosample collection is done in the SOC comparators after written informed consent. The same inclusion and exclusion criteria will apply in the parallel comparators under SOC as in patients participating in the SAVE trial. Data collection in these departments has been approved by the Ethics Committees of the participating hospitals. Propensity matching will be performed among comparators to the 130 patients enrolled in the SAVE trial, so as the 130 comparators will be fully comparable to all below criteria:

- Age
- Comorbidities, as expressed by the Charlson’s Comorbidity Index
- Admission severity scores namely pneumonia severity index (PSI), acute physiology and chronic health evaluation (APACHE) II score, SOFA score and WHO severity classification of COVID-19
- Co-administered treatment of azithromycin, hydroxychloroquine and dexamethasone

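### The SAP gives comparators no time zero: SAVE patients are followed from first dose, comparators are matched on admission severity, and the SRF comparison can be biased in either direction

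*Supplement*

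**What the plan says.** **SAVE patients.** The visit section of protocol version 3.0 defines Day 1: "This visit will take place on the morning of the day of the start of treatment with the study drug". Day 14 is counted from the same origin: "This visit will take place on the morning of the 14^th^ day from the start of treatment with the study drug". The endpoint is read on that clock: "The primary study endpoint is the rate of patients who will develop SRF (see Appendix V for definition) until day 14", with earlier death counted as an event.

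Entry follows consent, the exclusion and inclusion screens and a suPAR result (Screening for eligibility): "If suPAR is found ≥6 ng/ml, the patient can be enrolled in the study". The exclusion criteria under Study population bar "Presence of respiratory failure as defined in Appendix V", any pO2/FiO2 ratio below 150, and "Any need for CPAP or mechanical ventilation". Neither document limits the time from admission to screening or first dose.

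**Comparators.** The SAP takes concurrent registry patients on standard of care in eight Athens departments and applies the SAVE inclusion and exclusion criteria to them. It propensity-matches 130 of them to the first 130 SAVE patients. The severity variables are admission values: "Admission severity scores namely pneumonia severity index (PSI), acute physiology and chronic health evaluation (APACHE) II score", followed by SOFA and WHO class. The protocol's section on interim and statistical analysis lists the same admission scores. Days from admission to first dose is not a matching variable.

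**Analysis.** The SAP compares the primary outcome between groups by Fisher's exact test. It adds survival analysis, plus stepwise Cox regression for the primary outcome and 30-day mortality. No time origin is given for comparators in any of these.

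**The concern.** A SAVE patient has, by design, stayed free of SRF up to the day of first dose. A comparator who was eligible at admission and progressed a day later could stay in the comparator group and count as an event. A similar patient at a SAVE site who progressed before screening could not have been enrolled. Matching on admission scores cannot correct this, because what differs is the starting point of the clock and not the severity at admission.

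This matched comparison is the plan's only between-group test of the primary outcome. If time zero is left open, its result cannot be interpreted with confidence, and the choice of origin could be made after the data are seen.

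A related gap is that the Day 1 list and Appendix II schedule SOFA but do not name PSI, APACHE II, WHO class or admission date. SOFA is therefore a Day 1 value in SAVE, while the SAP calls for an admission value.

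**Working it through.** The plan gives no figure for this point, so there is none to reproduce. The check has two parts.

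**1. Timing rules side by side**

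| Item | SAVE | Comparators |
| --- | --- | --- |
| Eligibility day | Screening, before first dose | Not stated |
| SRF-free at start | Yes, at screening | Same criteria, day not stated |
| Start of 14-day clock | First dose | Not stated |
| Severity used in matching | Admission (only SOFA scheduled, on Day 1) | Admission |
| Days since admission | No limit, not matched | Not matched |

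The only timing anchor near the comparators is admission. The matching scores are admission values, and the assumed control SRF rate is tied to suPAR at admission.

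**2. Size and direction if comparators are followed from admission**

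Inputs:
- 14-day SRF risk from admission: 55% (protocol version 3.0, Number of patients). The SAP uses 60%.
- Drug effect: none.
- Lag *d* from admission to first dose: 1 or 2 days. This is an assumption; the documents give none.
- Hazard shape *k*: 0.5 to 1.5. This is an assumption; below 1 is front-loaded, 1 is constant, above 1 is rising.

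Formulas: cumulative hazard H(t) = −ln(0.45) × (t/14)^k = 0.7985 × (t/14)^k. The risk over 14 days from day *d*, given no event before it, is 1 − exp{−[H(14+d) − H(d)]}.

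Worked cases:
- k = 0.5, d = 1: H(15) = 0.8265 and H(1) = 0.2134, difference 0.6131, risk 1 − exp(−0.6131) = 45.8%.
- k = 1.5, d = 2: H(16) = 0.9756 and H(2) = 0.0431, difference 0.9325, risk 1 − exp(−0.9325) = 60.6%.

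Apparent SAVE rate against a comparator rate of 55%:

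| Shape k | d = 1 | d = 2 | Spurious difference (points) |
| --- | --- | --- | --- |
| 0.5 | 45.8% | 42.4% | 9.2 to 12.6 for anakinra |
| 0.6 | 48.7% | 46.0% | 6.3 to 9.0 for anakinra |
| 0.8 | 52.6% | 51.3% | 2.4 to 3.7 for anakinra |
| 1.0 | 55.0% | 55.0% | 0 |
| 1.2 | 56.6% | 57.7% | 1.6 to 2.7 against |
| 1.5 | 58.1% | 60.6% | 3.1 to 5.6 against |

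With d = 0 every row returns 55%. At the SAP's 60% the pattern is the same: shape 0.5 gives 50.5% and 46.9%, shape 1 gives 60.0%, and shape 1.5 gives 63.2% and 65.7%.

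**Effect on the test.** Suppose a share *q* of admission-eligible patients progresses before first dose, and ignore events after day 14 from admission. The apparent SAVE risk is then (p − q)/(1 − q). At p = 55% and 130 per group, the chance that Fisher's test shows a falsely significant benefit is 2.0% at q = 0, 4.7% at q = 5%, 10.7% at q = 10% and 40.8% at q = 20%. This model can only err towards the drug, because it leaves out the later days that SAVE patients are followed. It shows how sensitive the test is and says nothing about the sign.

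**The case against.** The strongest objection is that a missing definition is not a bias. Five points support it.

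- **Comparator clock.** Neither document says comparators are followed from admission. Admission appears as the timing of covariates and of the assumed control rate. This stands, so the bias is conditional.
- **Same criteria.** Comparators already in SRF, below pO2/FiO2 150 or needing ventilatory support on the day of assessment are removed. This stands in part. Applied at admission, the criteria still keep those who progress between admission and the matched patient's first dose.
- **Lag.** The suPAR test takes 20 minutes and treatment is meant to be early. Same-day dosing would make the bias close to nil. This stands as a limit on size, but nothing requires same-day dosing.
- **Status of the comparison.** The protocol's primary endpoint is the single-arm SRF rate, and the comparison with standard of care is secondary. This is correct, but the SAP tests the primary outcome between groups.
- **Unscheduled scores.** PSI, APACHE II and WHO class may come from hospital records, and no case report form is shown. That is fair, so this is a documentation gap and does not bear on time zero.

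A reader might go further and infer immortal-time bias that makes anakinra look better than it is. The documents do not support that. SAVE time before first dose is not credited to the drug, because follow-up starts at first dose. The possible fault is a misaligned time zero with selection of patients still event-free. Its sign depends on a hazard shape the documents do not give. The largest pro-drug figures need shape 0.5, under which 19% of eligible patients progress within one day and 26% within two; nothing in the documents supports such rates.

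**Conclusion.** The omission is real. The two groups have no common time zero, and applying the same criteria does not supply one. What follows from it is conditional. If comparators are followed from admission and first doses come 1 to 2 days later, a 55% control risk and no drug effect give an apparent SAVE rate between about 42% and about 61%. That is a spurious difference from about 13 points in favour of anakinra to about 6 points against it. The planned effect is 15 points in the SAP and 20 in the protocol. Under constant hazard or same-day dosing the bias is nil. The lag, the hazard shape and the comparators' starting day are all assumptions, so neither direction nor size is established. The point still merits a change, because the plan as written permits a material bias in its key comparison and a better method costs little.

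**What to change.** In the SAP:

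1. Give each comparator an index day equal to the hospital day of the matched SAVE patient's first dose.
2. Require the comparator to be alive on that day and to meet every inclusion and exclusion criterion, including SRF-free status. State which suPAR measurement counts if the registry has none from that day.
3. Match on severity at the index day where the registry holds it. Otherwise match on admission scores plus days from admission.
4. Count 14-day SRF or death, 30-day mortality and survival time from the index day in both groups.

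For SAVE patients, record the admission date and the scores used in matching.

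The cost is SAP wording, some programming and a few added fields. The downside is that comparators who progressed before the index day leave the pool, which may make 130 matches harder to find. The estimate then applies to patients still eligible on the day of first dose, which is the population SAVE enrols.

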# BACKGROUND

The major hurdle of COVID-19 is the early recognition of the patients at high risk for the development of severe respiratory failure (SRF). If this can be achieved early, then appropriate immunomodulatory treatment may be administered to prevent development of SRF. This scenario is extremely visionary since it prevents the development of the major fatal consequence of Covid-19 but also alleviates the heavy medical and financial burden of Intensive Care Unit (ICU) admission.

Current evidence suggests that SARS-CoV-2 activates endothelial function which leads to over-production of D-dimers^1,2^. uPAR (urokinase plasminogen activator receptor) is anchored to the cell membranes of the lung endothelial cells. As result of the activation of kallikrein, uPAR is cleaved and enters the systemic circulation as the soluble counterpart suPAR^3^. Preliminary unpublished data from 57 Greek patients hospitalized after March 1^st^ 2020 in Greek hospitals due to pneumonia by confirmed SARS-CoV-2 infection showed that those with suPAR admission levels ≥ 6 ng/ml had greater risk for the development of SRF within 14 days than patients with suPAR less than 6ng/ml (Figure 1). The sensitivity of suPAR to detect these patients was 85.9% and the positive predictive value 85.9%. It needs to be outscored that all 21 Greek patients with suPAR≥ 6ng/ml were under standard-of-care treatment, which at that moment consisted of hydroxychloroquine and azithromycin. These data were confirmed in 15 patients hospitalized for pneumonia by SARS-CoV-2 in Rush Medical Center at Chicago^4^. A recent publication of 881 patients from the ISIC database verified these results^5^.

This prognostic ability of suPAR for unfavourable outcome is not presented for the first time; in the TRIAGE III trial that was conducted among 4,420 admissions in the emergency department in Denmark the interquartile range of suPAR was between 2.6 and 4.7 ng/ml in 30-day survivors and between 6.7 and 11.8 ng/ml in 30-day non-survivors^6^. Previous data from the Hellenic Sepsis Study Group on 1,914 patients clearly shows a high prognostic utility of admission suPAR for 28-day mortality^7^.

[figure not shown]

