# NUMBER OF PATIENTS

The study power calculation is based on the hypothesis that 55% of patients with lower respiratory tract infection due to COVID-19 and suPAR≥6 ng/ml upon hospital admission, will develop SRF. To decrease this to 35% with power of 90% at a 5% level of significance, two hundred sixty (260) patients need to be enrolled. Taking into consideration, the single-arm study design, 500 patients should be enrolled to make results more robust.

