# INTERIM AND STATISTICAL ANALYSIS

An interim analysis will be conducted after completion of the 30-day follow up of the first 130 patients, i.e. 50% of the number of patients needed to be enrolled as calculated by power analysis. As comparators will be used patients hospitalized with pneumonia by the SARS-CoV-2 virus in other departments of Greek hospitals in which full data collection is performed by the Hellenic Sepsis Study Group, after written informed consent. Data collection in these departments has been approved by the Ethics Committees of the respective hospitals. For the purpose of this analysis, patients receiving standard-of-care treatment (SOC) will be selected among the total patients whose data are fully collected in order to fulfill the same inclusion and exclusion criteria as patients enrolled in the SAVE trial. Propensity matching will be performed among comparators and 130 patients enrolled in the SAVE trial, so as the 130 comparators will be fully comparable to all below criteria:

- Age
- Comorbidities, as expressed by the Charlson’s Comorbidity Index
- Admission severity scores namely pneumonia severity index (PSI), acute physiology and chronic health evaluation (APACHE) II score, SOFA score and WHO severity classification of COVID-19
- Co-administered treatment, such as azithromycin and dexamethasone

The primary endpoint will expressed as percentage and 95% confidence intervals. Comparisons with historical cases will be done by the Fisher exact test. Any p-value below 0.05 will be considered significant.

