Primary outcome and binary secondary outcomes as well as serious adverse event and adverse event rates between the two groups will be expressed as percentages and will be compared by the Fisher exact test, calculating also the respective odds ratios. The time to an event will be compared between the two groups by survival analysis. Stepwise Cox regression analysis will be conducted for the primary outcome and 30-day mortality. Quantitative secondary outcomes will be expressed as median values with respective interquartile range and will be compared by the Mann-Whitney U test.

The cost of hospitalization will be measured by adding the itemized cost of stay, drugs, and interventions and will be expressed as median with respective interquartile range. Salaries of nurse and medical stuff will not be included. Cost comparison will be done by the Mann-Whitney U test.

Qualitative baseline characteristics will be expressed as frequencies and percentages and compared by the Fisher exact test. Quantitative baseline characteristics will be expressed as mean values with standard deviation if following a normal distribution or median values with quartiles if following linear distribution. Comparisons of quantitative baseline characteristics will be done by the Student’s t-test or by the Mann-Whitney U test respectively. Paired comparisons will be done by the Wilcoxon’s rank-signed test. Non-parametric correlations will be done according to Spearman.

Analysis will be conducted with SPSS Version 25.0. All P values will be two-sided. Any P value <0.05 will be considered as statistically significant.

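### The propensity match leaves out the suPAR level and sets no baseline window for co-treatments, so avoidable bias could remain in the comparison with standard care

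*Supplement*

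**What the plan says.** The matching list is in the SAP (5 October 2020) and, almost identically, in protocol v3.0 under Interim and Statistical Analysis. It covers age, the Charlson index, four severity measures taken at admission (PSI, APACHE II, SOFA, WHO class) and, in the SAP, "Co-administered treatment of azithromycin, hydroxychloroquine and dexamethasone". The protocol's drug item is open-ended and names azithromycin and dexamethasone as examples. Neither list contains the suPAR value or the admission date. Both specify the match for the interim analysis of the first 130 patients.

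Other relevant text:

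- **suPAR.** The protocol's Background reports that "those with suPAR admission levels ≥ 6 ng/ml had greater risk for the development of SRF within 14 days" than patients below the threshold. Screening for Eligibility describes the assay as quantitative and accurate from 2 to 15 ng/ml. The SAP applies the same entry criteria to comparators, so each needs a suPAR result of at least 6 ng/ml, and it states that biosamples are collected from them.
- **Co-treatments.** The protocol's visit lists for days 2 to 6 and 8 to 10 call for "Recording of co-administered drugs, absolute blood cell count and differential (if available) and biochemistry (if available". Co-administered drugs are also recorded on days 1, 7 and 14. The Synopsis allows all other drugs.
- **Comparators.** The SAP takes parallel comparators from the same period. The protocol says "Comparisons with historical cases will be done by the Fisher exact test".
- **Analysis.** The SAP compares the two groups on the primary outcome by the Fisher exact test. It adds a stepwise Cox model whose covariates are not named.

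**The concern.** The primary endpoint is a single-arm rate; the only controlled evidence is the secondary comparison with registry patients. In the Fisher test the match is the sole control of confounding, so the list of matching variables matters.

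Two features of the list stand out. First, the variable on which patients are selected is used only as a cut-off. Two groups can both lie at or above 6 ng/ml and still differ in level. If SRF risk rises with suPAR above 6, that difference would be read as a drug effect or would hide one.

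Second, the severity scores are tied to admission but the co-treatments are not tied to any time. Taken literally, the item lets an analyst match on a drug started on, say, day 5 because the patient was getting worse. Such use is partly a result of the early course that anakinra is meant to change, and matching on it can remove part of the effect or otherwise distort it.

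**Working it through.** The plan gives no figure for balance or residual bias, so there is none of its own to reproduce on this point. The planning rates serve as anchors. The SAP has the "hypothesis that 60% of patients with lower respiratory tract infection due to COVID-19 and suPAR≥6 ng/ml upon hospital admission will develop SRF" and a target of 45%; the protocol assumes 55% and a target of 35%. The effect sought is therefore 15 or 20 points. (Whether the stated 260 patients follow from these rates is a separate question and does not enter here.)

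**1. suPAR imbalance.** Assumed inputs, not in the documents: a mean gap of 1 ng/ml between groups, and an SRF odds ratio (OR) per ng/ml of 1.1, 1.2 or 1.3. Base rate: 45%, the SAP's target.

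Shift = expit(logit 0.45 + ln OR) − 0.45. Base odds = 0.45/0.55 = 0.818.

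| OR per ng/ml | New odds | New rate | Shift |
|---|---|---|---|
| 1.1 | 0.900 | 47.4% | 2.4 points |
| 1.2 | 0.982 | 49.5% | 4.5 points |
| 1.3 | 1.064 | 51.5% | 6.5 points |

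Starting from the SAP's 60% (odds 1.5) and dividing by the OR gives 57.7%, 55.6% and 53.6%, shifts of 2.3, 4.4 and 6.4 points. The choice of base rate hardly matters.

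**2. What such a shift does to the test.** Simulated Fisher exact tests, 130 v 130, comparator SRF 60%, no drug effect, two-sided 5% (the SAP states "All P values will be two-sided"), counting significant results in favour of anakinra:

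| Spurious difference | Significant for anakinra |
|---|---|
| 0 points | 1.9% |
| 2 points | 4.0% |
| 5 points | 10% |
| 10 points | 33% |

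This is the case in which SAVE patients have the lower suPAR. With the opposite imbalance, a real effect would be understated.

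**3. Matching on a drug started after day 1.** Inputs: true SRF 60% v 45% (SAP). Assumed: SRF is 80% in patients who worsen early and 20% in the others, the co-treatment itself does not alter SRF, and its use depends only on worsening.

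Share worsening = (SRF rate − 0.20)/(0.80 − 0.20): 0.667 in comparators, 0.417 in SAVE.

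Example with the drug started in 80% of worsening and 20% of other patients:

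- Comparators: SRF is 73.3% among users and 40.0% among non-users.
- SAVE: 45% are users, with SRF 64.4%; 55% are non-users, with SRF 29.1%.
- Matched difference = 0.45 × (73.3 − 64.4) + 0.55 × (40.0 − 29.1) = 4.0 + 6.0 = 10.0 points, against a true 15.0.

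| Started if worsening / if not | Matched difference | Share of effect lost |
|---|---|---|
| 50% / 50% | 15.0 | 0% |
| 60% / 40% | 14.5 | 4% |
| 70% / 30% | 12.8 | 14% |
| 80% / 20% | 10.0 | 33% |
| 90% / 10% | 5.8 | 61% |

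The loss appears only if later use is counted and depends on worsening.

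**The case against.** The plan controls more than the omissions suggest, and most of the case on the other side stands.

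- **suPAR.** Both groups must be at or above 6 ng/ml, and four severity measures are matched. The COVID-19 evidence in the Background compares patients above and below the threshold. It shows no gradient in SRF risk above 6, still less one that remains after those severity measures. The suPAR quartiles cited from an emergency-department trial concern 30-day death in general admissions. Nor is a single pair with unequal suPAR a bias in itself, since propensity matching aims at balance between groups.
- **Co-treatments.** The SAP does not say that later use counts. The item follows the admission scores in a list of matching variables and can be read as baseline use. This is a gap in definition, not a stated rule.
- **Calendar time.** A reader might infer from the protocol's word historical that the comparison mixes periods of care. The documents do not support that: the SAP restricts comparators to the same period, and the protocol sentence is carried over unchanged from v1.0, while the v3.0 secondary endpoint already refers to standard-care comparators. The matched drugs may also act as a partial proxy for date. Only drift within a study of up to 24 months is left, and nothing in the documents sizes it.
- **Cox model.** It might adjust for suPAR, but its covariates are unnamed and chosen stepwise, so it cannot be relied on for this.

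What remains is that a quantitative risk marker needed for eligibility in both groups is left out of the model, and that one matching item has no time reference.

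**Conclusion.** The point holds as a gap worth closing: should fix, medium confidence. The suPAR level is absent from both matching lists, eligibility balances only the threshold, and the Fisher test adjusts for nothing further. Under the assumed 1 ng/ml gap and ORs of 1.1 to 1.3, the SRF rate moves by 2.4 to 6.5 points at a 45% base rate, against a planned effect of 15 (SAP) or 20 (protocol) points. The direction depends on which group has the higher suPAR.

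The co-treatment item could distort the effect if drugs started after day 1 because of worsening were counted. The distortion is towards no effect if the drug does not itself alter SRF; otherwise the direction can differ. Under the assumptions shown, the loss runs from nothing to 61% of the effect.

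A reader might go further and conclude that the match is biased as written, or that the main prognostic factor is uncontrolled. Neither follows: the documents show no imbalance above 6 ng/ml, no risk gradient there, and no rule that counts later drug use.

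**What to change.** In the SAP, and in the protocol's Interim and Statistical Analysis section to match:

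1. Add baseline suPAR level to the propensity model, with values above the 15 ng/ml assay limit set to 15.
2. Count only co-treatments in use on or before day 1, or on or before the comparator's equivalent index day, which the SAP should define. Use the same list of drugs in both documents.
3. Include admission date or a calendar stratum if the comparator pool allows. This has lower priority, since the SAP already restricts comparators to the same period.
4. Report balance on these variables after matching.
5. Replace the protocol's reference to historical cases with the SAP's parallel comparators.

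The cost is wording and a revised model, using data that the plan already collects or needs for eligibility. The downside is that some SAVE patients may lose a close match. The documents do not give the size of the comparator pool, so whether 130 matches would still be reached cannot be judged from them.
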